### Data collection, management, and analysis

#### Data collection methods {18a}

Once the patient enters the study, he or she will be in touch by telephone with the study’s clinic. The clinic provides the necessary training over the phone to the patient to get acquainted with the symptoms of COVID-19. In case of suspicious symptoms or contact with a suspected patient or patient with definite COVID-19, the patient will be invited to the clinic and will be examined clinically and paraclinically (Additional file 1). Besides, all patients at each visit for cancer treatment will be evaluated by their treating physician for signs of COVID-19. If there is any clinical suspicion, the patient is referred to the clinic. The research team was invited to a coordination meeting to review the study protocol. Predictable limitations were discussed and questions were answered. The outcome assessors were trained to reduce any interobserver variations.

#### Plans to promote participant retention and complete follow-up {18b}

Monitoring of patients’ compliance in the study is done in such a way that these patients are either hospitalized or visit every 2 to 3 weeks and therefore are regularly supervised. At the same time, the patient does not have to stay in the study and also does not need to provide any reason to leave it. Explanations are given to the patient about the safety of the drug and additional care that the research team provides would increase patients’ cooperation. There will be no outcome data collected for participants who discontinue or deviate from intervention protocols.

#### Data management {19}

All information collected, including patient’s history and examinations, and their paraclinical information are recorded in the form of papers and electronic files by the assessors. These files are stored in a locked room in the hospital archives for possible future use. The paper files were transferred by the principal investigator to the trial office for data entry. All data were transformed and coded into an SPSS file by an anonymized statistician. This file is also stored in encrypted form on the clinic computer. Before statistical analysis, the SPSS file was checked for data value ranges to find any possible errors.

#### Confidentiality {27}

In the data collection process, each patient is assigned a code. Forms containing the name and code of each patient are available only to the principal researcher of the study and are kept in accordance with the research protocols and the ethics committee. In the process of publishing the results, no names of patients are mentioned.

#### Biological specimens {33}

Biological samples of patients are kept in the Cohort center of Mashhad University of Medical Sciences. This center is equipped for research approved by this university.

Specific COVID-19 antibody test kits were not yet available at the start of this study. Therefore, 5 ml of patients’ blood was taken at the beginning of the study, and after centrifugation, its plasma was kept at minus 20 °C until the antibody testing. From July 2020, when COVID-19-specific antibody testing became available, storage of patients’ plasma samples was eliminated.

### Statistical methods

#### Statistical methods for analyzing primary and secondary outcomes {20a}

Data analysis will be performed using SPSS software version 16 (SPSS Inc., Chicago, IL, USA). Quantitative variables will be described by mean and standard deviation and qualitative variables will be described by frequency and percentage. Quantitative variables between control and intervention groups will be compared by Student’s *T*-test or Mann-Whitney test.

The comparison of qualitative variables between the two groups will be performed by the chi-square test and Fisher’s exact test. For intragroup comparisons, paired *T*-test or Wilcoxon test will be used. All tests will be two-tailed and the significant level will be considered less than 0.05.

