### Criteria for discontinuing or modifying allocated intervention {11b}

During the study, patients will be monitored for cardiac complications by performing an electrocardiogram (ECG) in the first visit and each chemotherapy session or at least once, every 4 weeks. The most important point in ECG is to calculate corrected QT interval; if the interval is longer than 500 ms, the drug will be discontinued, a drug complication is recorded, and the patient referred to a cardiologist.

At the beginning of the study, a comprehensive history of ophthalmologic problems will be obtained. All patients will be evaluated for any new visual disturbances during the study. In case of new visual disturbances, an examination by an ophthalmologist is warranted and a drug complication is recorded. Since the ocular side effects of HCQ have been reported in long-term use, often after 12 months, periodic examination in asymptomatic patients was not considered.

All patients with hydroxychloroquine drug side effects were excluded from the study in addition to the necessary treatment and compensation measures.

There is not any evidence-based recommendation for baseline cardiac function assessment and ophthalmologic examination in short-term and low dose use of hydroxychloroquine.

Other less common side effects such as hematologic, skin, and gastrointestinal complications are monitored by treating physician. Besides, an Internist is introduced to patients by researcher team just to answer the patients concerns about the study medication or to make an out-of-schedule visit if needed.

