### Outcome {12}

The primary endpoint is the comparison of the COVID-19 incidence in the two groups of study. Patients are assessed for the outcome for the entire duration of 8 weeks of drug use and up to 2 weeks after stopping the drug. The secondary endpoint is to evaluate disease severity in both arms. Criteria used to assess disease severity include clinical and paraclinical. Clinically, what shows the severity of the disease is the degree of dyspnea and decreased arterial oxygen saturation. The amount of supplemental oxygen required by the patient and the method of its administration, i.e., the type of mask and invasive or non-invasive ventilation, are also recorded. The best paraclinical criterion for determining the severity of the disease in cancer patients is the extent of pulmonary involvement on lung HRCT scan. Other factors that help include lymphopenia, the rate of increase in inflammatory markers, the length of hospital stay, and the rate of intensive care unit (ICU) stay.

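### Within-arm paired tests are planned at the 0.05 level without a descriptive label; for repeated measures such as QTc they cannot separate a drug effect from change shared by both arms

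*Protocol article*

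**What the plan says.** Section {20a} covers the analysis of primary and secondary outcomes. It plans between-arm tests for both kinds of variable:

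- Quantitative: "Quantitative variables between control and intervention groups will be compared by" Student's t or Mann-Whitney.
- Qualitative: "The comparison of qualitative variables between the two groups will be performed by the chi-square test" and Fisher's exact test.

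It then adds within-arm tests. The sentence beginning "For intragroup comparisons, paired" names a paired t-test or Wilcoxon test, but no variable, time points or purpose. The closing sentence applies to every test in the section: "All tests will be two-tailed and the significant level will be considered less than 0.05".

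Section {12} defines the endpoints: "The primary endpoint is the comparison of the COVID-19 incidence in the two groups of study", and "The secondary endpoint is to evaluate disease severity in both arms". Among the supporting severity factors it lists lymphopenia and "the rate of increase in inflammatory markers".

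Section {11b} provides for "performing an electrocardiogram (ECG) in the first visit and each chemotherapy session", or no less often than every 4 weeks, with corrected QT as the main reading. Sections {11a} and {6b} state that both arms receive study medication on top of cancer treatment.

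**The concern.** A paired test in one arm asks whether that arm changed over time. In this trial both arms can change because of chemotherapy, illness or the passage of time, and the placebo arm is there to remove that shared change. A within-arm p-value leaves it in.

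The usual consequence is the comparison of two p-values: one arm reaches significance, the other does not, and the contrast is taken as a difference between treatments. It can also give false reassurance, when a shared change in the opposite direction hides a drug effect within the treated arm.

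Because these tests are pre-specified at the same level as the randomised comparison, and nothing says which result governs, section {20a} leaves room for that reading on safety or secondary quantities.

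**Working it through.** **Which variables the tests can apply to**

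- *Primary endpoint.* COVID-19 is a new binary event. Section {10} excludes patients with signs or symptoms before entry, so there is no before-after pair of quantitative values. Paired t and Wilcoxon tests do not apply.
- *QTc.* Section {11b} gives an entry ECG and repeated later ECGs, so pairs exist in both arms.
- *Lymphocytes and inflammatory markers.* Section {12} uses these to grade severity in patients who develop COVID-19. Sections {11a} and {18a} place the work-up at referral to the clinic. The visible text shows no entry value.

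**Inputs**

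- Arm size n = 30, from section {14}. The plan gives no figure of its own for the within-arm tests. The 30 serves here only as the largest number of complete pairs per arm; its derivation is a separate matter.
- Two-sided level 0.05, from section {20a}.
- Assumption, not in the documents: the same mean change in both arms, 0 to 0.8 SD of the within-patient change, and no drug effect.

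**Formulas**

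Write δ for the shared change and τ for the drug effect. The mean within-arm change is δ + τ under hydroxychloroquine and δ under placebo. The paired test in the treated arm tests δ + τ = 0. Only the between-arm difference isolates τ.

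With d = δ/SD and τ = 0, the chance p that one arm's paired t-test is significant comes from the non-central t distribution with 30 − 1 = 29 degrees of freedom and non-centrality d√30. The arms are independent, so:

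- exactly one arm significant: 2p(1 − p)
- hydroxychloroquine arm only: p(1 − p)

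| Common change d (SD) | p, one arm | Exactly one arm | Hydroxychloroquine only |
|---|---|---|---|
| 0 | 0.050 | 9.5% | 4.8% |
| 0.2 | 0.185 | 30.2% | 15.1% |
| 0.3 | 0.355 | 45.8% | 22.9% |
| 0.4 | 0.563 | 49.2% | 24.6% |
| 0.5 | 0.754 | 37.1% | 18.5% |
| 0.8 | 0.988 (simulated) | 2.4% | 1.2% |

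For example, at 0.4 SD: 2 × 0.563 × 0.437 = 0.492. The ceiling is 50%, reached when p = 0.5.

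**Check by simulation** (40,000 trials per setting, 30 per arm, no drug effect)

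| d (SD) | Exactly one arm | Hydroxychloroquine only | Between-arm t-test of change |
|---|---|---|---|
| 0 | 9.4% | 4.7% | 4.8% |
| 0.2 | 30.3% | 15.3% | 5.0% |
| 0.358 | 49.8% | 24.9% | 5.0% |
| 0.5 | 36.8% | 18.4% | 5.1% |
| 0.8 | 2.3% | 1.1% | 4.8% |

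The between-arm test holds its 5% level whatever the shared change.

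**Severity markers**

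At the top of the incidence range in section {14}, 8%, and with the assumed 40% reduction (0.08 × 0.6 = 0.048), expected cases are 30 × 0.08 = 2.4 and 30 × 0.048 = 1.4. The smallest two-sided exact p of a Wilcoxon signed-rank test on five pairs is 2/2⁵ = 0.0625, and it is larger with fewer pairs. With so few cases that test cannot reach 0.05 in either arm, so the rates in the tables do not carry over to these markers.

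**The case against.** The strongest reply is that section {20a} already plans the randomised comparison for both types of variable, and a between-arm t-test of change fits its wording. This stands. A reader might infer that the plan ignores the placebo group or discards the control; the between-arm sentences in the same section rule that out.

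A reader might also infer that within-arm changes will be reported as an effect of hydroxychloroquine. No section says so, or makes significance in one arm only a criterion. Section {7} states the aim as a comparison of two groups. The misreading is a risk left open, not a stated intention.

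QTc is a monitoring variable with a discontinuation threshold, not an endpoint in section {12}, and no test of its mean change is announced. This also stands. QTc is named here because it is the one measure in the visible text that the unspecified paired tests clearly fit.

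Finally, an unadjusted between-arm comparison is valid under randomisation, and a condensed article need not spell out covariates. The absence of ANCOVA is therefore not an error. What the reply does not remove is a test that the article does state, at the inferential level, which cannot answer a question about treatment.

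**Conclusion.** The point holds in a limited form. The within-arm tests are planned at two-sided 0.05 without a descriptive label, and no result from them can be attributed to the drug. They leave the primary endpoint untouched and concern safety and secondary quantities only.

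For a measure with 30 complete pairs per arm, such as QTc, a shared change of 0.2 to 0.5 SD would make exactly one arm significant in about 30% to 49% of trials with no drug effect. In half of those (about 15% to 25%) it would be the hydroxychloroquine arm. A between-arm test gives 5%.

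These rates rest on an assumed common change that the documents do not supply. Exactly one arm is significant in about 10% of trials at zero change and about 2% at 0.8 SD. They also assume no dropout; section {20c} excludes dropouts, so fewer pairs may be available. The point is minor in consequence but costs almost nothing to correct.

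**What to change.** Delete the intragroup-test sentence in section {20a}, or replace it with a statement that within-arm change is described without tests.

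State that every treatment conclusion rests on the between-arm comparison. For QTc, compare the arms at a named follow-up ECG by ANCOVA with the entry value as covariate, and report the difference with a 95% confidence interval. The adjustment is an improvement in precision rather than the repair of an error.

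Extend the same approach to lymphocyte count or inflammatory markers only if entry values were collected.

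The cost is one or two sentences in the analysis section. For QTc no new data are needed, because the entry and later ECGs are already in the schedule. For the other markers the visible text does not show that this is so.

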#### Methods for additional analyses {20b}

There are no subgroup analyses planned.

#### Methods of analyses to handle protocol non-adherence and statistical methods to handle missing data {20c}

The analysis is based on per-protocol and any dropout or group crossing will be excluded from the final analysis. The probable missing data will not be imputed.

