### Strategies to improve adherence to intervention {11c}

The drug is taken under the supervision of a nurse in hospitalized patients. The amount of medication used in the out-patient setting is regularly checked, just by history taking, at each chemotherapy visit by the treatment team. Also, a member of the research team checks the regular use of the drug at least once by phone between every two visits of the patients.

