#### Conditions for unblinding {17b}

Whenever a patient experiences any attributable drug side effects, her/his information will be recorded, the intervention would be stopped and necessary care will be applied. Then his/her study group will be revealed to the treating physician.

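### The only stated analysis is per-protocol and outcomes are not collected after stopping or deviating, so post-randomisation exclusions can bias the primary comparison

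*Protocol article*

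**What the plan says.** All references are to the protocol article.

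- Section {20c} fixes the analysis set: "The analysis is based on per-protocol and any dropout or group crossing will be excluded from the final analysis". It adds: "The probable missing data will not be imputed". No intention-to-treat or sensitivity analysis is named anywhere.
- Section {18b} fixes data collection: "There will be no outcome data collected for participants who discontinue or deviate from intervention protocols".
- Section {11b}: "All patients with hydroxychloroquine drug side effects were excluded from the study". It also sets an ECG criterion for stopping the drug.
- Section {17b}: after an attributable side effect the intervention stops, and "Then his/her study group will be revealed to the treating physician".
- Section {10} lists, among the exclusions, COVID-19 arising in the first two weeks after entry.
- Section {12} has patients assessed for the whole 8 weeks of drug use and up to 2 weeks afterwards, with no exception for those who stop.
- Section {11c}: outpatient medication use is "regularly checked, just by history taking, at each chemotherapy visit by the treatment team". Inpatient doses are supervised by a nurse, and the research team also checks by phone between visits.

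**The concern.** This is a placebo-controlled superiority trial of prevention. Its protection against confounding comes from comparing the groups as randomised. Sections {20c}, {18b} and {11b} together replace those groups with the patients who stayed on the assigned tablets without a recorded side effect.

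Two features make it plausible that the exclusions differ between arms.

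- The exclusion in {11b} is for side effects of HCQ, so it should fall mainly on the active arm. Blinding does not prevent this, because the drug itself causes the exclusion.
- The Limitations section raises intolerance in patients with nausea and vomiting on chemotherapy days, which plausibly goes with intensity of cancer treatment. Section {9} deliberately mixes cancers at low and high risk of COVID-19. Losing more high-risk patients from one arm would unbalance the arms on the outcome itself.

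The data-collection rule makes the problem harder to repair. An analysis plan can redefine a population, but it cannot analyse outcomes that were never sought.

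**Working it through.** **Inputs.** Section {14}: COVID-19 incidence of 1 to 8%, about a 40% decrease, 30 per arm. I read the decrease as relative, because a fall of 40 percentage points from 1–8% is impossible. The protocol gives no rates of discontinuation, deviation or side effects, so every exclusion rate below is assumed.

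**The plan's own figure.** The 30 per arm cannot be reproduced from these inputs: 8% v 4.8%, two-sided 5%, 80% power needs 918 per arm. That is a separate matter, and nothing below depends on it. I use 30 per arm as the planned size.

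**Step 1: expected cases at 30 per arm.**
- At 8%: placebo 30 × 0.08 = 2.4; HCQ 30 × 0.08 × 0.6 = 1.44; total 3.84.
- At 1%: 0.3 + 0.18 = 0.48.

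**Step 2: effect of one exclusion.**
- All randomised: (2/30)/(3/30) = 0.67, Fisher p = 1.0.
- One HCQ case excluded after stopping tablets: (1/29)/(3/30) = 0.34, Fisher p = 0.61.

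The estimate halves, and both results are non-significant.

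**Step 3: can significance change?** At 30 v 30 the smallest significant split is 6 v 0 (p = 0.024); 5 v 0 gives p = 0.052. That is more cases than the 3.84 expected. At higher incidence it can happen: 6/30 v 1/30 gives p = 0.103, and 6/30 v 0/29 gives p = 0.024. But 6/30 is a 20% placebo incidence, outside the stated range.

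**Step 4: expected bias if the drug does nothing.** Let a share d of the HCQ arm be excluded, with risk r times that of the patients retained, and nobody excluded from placebo. The expected per-protocol relative risk is 1/(1 − d + d·r). Analysed as randomised, it is 1.00.

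| d (assumed) | r (assumed) | Per-protocol relative risk |
|---|---|---|
| 10% | 2 | 1/1.1 = 0.91 |
| 20% | 3 | 1/1.4 = 0.71 |
| 20% | 5 | 1/1.8 = 0.56 |
| 30% | 5 | 1/2.2 = 0.45 |
| 20% | 0.5 | 1/0.9 = 1.11 |

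The last row shows that the direction can reverse if the excluded patients are at lower risk. Exclusions in both arms shrink the bias: with r = 3, 20% excluded from HCQ and 10% from placebo, the ratio is 1.2/1.4 = 0.86.

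A milder pattern: half the patients at 12% risk and half at 4%, with 40% of high-risk HCQ patients and 10% of everyone else excluded. HCQ risk is (0.6 × 0.12 + 0.9 × 0.04)/(0.6 + 0.9) = 0.072, against 0.080 for placebo, a ratio of 0.90.

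**Step 5: precision.** Excluding 10%, 20% or 30% leaves 27, 24 or 21 per arm.

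**Step 6: what unknown outcomes cost.** Illustration: 3 of 30 HCQ patients (10%) have no outcome and the rest show 1/27 v 3/30. Best case is 1/30 v 3/30, ratio 0.33. Worst case is 4/30 v 3/30, ratio 1.33. Three unknown outcomes span benefit and harm.

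**The case against.** The strongest reply is that little turns on this at the plan's own rates. With about 4 cases expected, neither analysis is likely to be significant. The assumed biases, particularly the ratio of 0.90, are small beside sampling error. This part stands: a reader might infer that the exclusions will decide the primary result, but Step 3 does not support that for incidence of 1–8%. What changes is the estimate.

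Other stronger readings also lack support.

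- A reader might suppose that a placebo patient given HCQ for suspected COVID-19 would be deleted as a crossover. The protocol provides for no such treatment, does not define group crossing, and in section {15} says HCQ was excluded from COVID-19 treatment.
- A reader might infer that adherence rests on history alone. Section {11c} says so only of outpatients; nurse supervision and phone checks are also described.
- A reader might take intolerance as expected at some rate. The Limitations section calls it a concern, gives no rate, and says the dose was chosen with it in mind.
- A reader might conclude that an analysis as randomised can never be recovered. Section {18b} says patients are in hospital or seen every 2 to 3 weeks, {18a} has treating physicians look for COVID-19 at each visit, and {19} says files are stored. Some outcomes may be found, though not necessarily with the repeated PCR tests of section {11a}.

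Nor can the point be left to an unseen analysis plan. The protocol states both the analysis set and the rule against collecting outcomes.

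**Conclusion.** The point holds. As written, the only stated analysis is one that randomisation does not protect, and {18b} withholds the data needed for one that is. Sections {12}, {11b} and {18b} also disagree on whether patients who stop are followed for the outcome, and must be reconciled.

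The size is conditional. One excluded case can move the relative risk from 0.67 to 0.34 without either result being significant. For an inert drug, the assumed scenarios give ratios from 0.45 to 1.11 instead of 1.00. These rest on assumed exclusion rates and risks. That exclusions fall mainly on HCQ follows from the wording of {11b}, but how unequal they are is unknown. Because the defect affects the validity of the only primary analysis, it should be corrected before the data are analysed.

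**What to change.** 1. **Primary analysis (section {20c}).** Include all randomised patients in the arm assigned, whatever their adherence, side effects or crossover. Keep per-protocol as supportive only.
2. **Early cases (section {10}).** Reconcile this with the exclusion of COVID-19 in the first two weeks. If that exclusion is kept, apply it identically and blind to arm in both groups, and add a sensitivity analysis that includes those cases.
3. **Outcome collection (section {18b}).** Replace the sentence so that outcomes to week 10 are sought for everyone who has not withdrawn consent. Section {15} ends recruitment in January 2021 and the trial status is dated 26 March 2021. Anyone entered by 15 January had therefore completed 10 weeks, and an entrant on 31 January would finish on 11 April. Continue follow-up for anyone still in the window; for the rest, make a best-effort search of hospital and clinic records. The searcher should not know the arm, so should not be a treating physician to whom it was revealed under {17b}.
4. **Unknown outcomes.** Report best-case and worst-case bounds, and exclusions by arm with reasons.

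**Cost.** Revised wording and a record search for those of the planned 60 patients who stopped or deviated. The search is real work, and records may lack the full PCR work-up, so some outcomes will stay unknown and the bounds may be wide. No dose or clinical rule needs to change.
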